### Randomization

Prior to enrolment, all inclusion and exclusion criteria will be thoroughly assessed. Eligible participants will be randomly assigned to one of two parallel groups using **block randomization with a fixed block size of four**, to ensure a progressive balance between arms throughout the inclusion period.

The randomization sequence was generated using a **table of random numbers** extracted from the reference textbook L’essai thérapeutique chez l’homme by Schwartz D et al, [7]. Allocated study subjects were randomly assigned by, using simple 1:1 non-stratified sequence and a block size of 4 [7].

Allocation was implemented sequentially, according to the randomization list, by a team member **not involved in outcome assessment**, in order to maintain **allocation concealment** and minimize the risk of selection bias.

The timeline for enrolment, intervention and assessments is outlined in the SPIRIT schedule of events in Fig 1

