### Blinding

The study will follow the principles of the double blinding Randomized Controlled trials [8], which is specifically intended to minimize bias in outcome assessment and data analysis.

To maintain blinding integrity and minimize bias, the participant and the assessor of the postoperative pain were blinded for the allocation. Only the surgeon, the anesthetist and the operating room nurse responsible for opening the allocation envelope and administering the assigned intervention will be aware of the group assignment. These persons will not be involved in outcome assessment, clinical follow-up, or data analysis. The outcome assessor will be a trainee resident. All outcome assessors, trained residents not involved in randomization or intervention delivery, will remain blinded to group allocation throughout the study. Similarly, data analysts will be blinded to treatment assignment to ensure objectivity in statistical analyses and interpretation of results. Anesthetist and surgeon will be explicitly instructed not to disclose their group allocation to any member of the clinical or research team involved in follow-up or outcome assessment. This approach is designed to preserve the integrity of the blinding process and uphold the internal validity of the trial.

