#### Trial implementation and coordination.

The rigorous implementation of this trial relies on strict protocol adherence clearly defined roles and standardized procedures to ensure methodological integrity and internal validity. Prior to enrolment, all department B of general surgery medical and paramedical staff will be trained on the study protocol and data collection methods during dedicated briefing sessions.

The randomization sequence will be generated by (CD) not involved in recruitment, intervention delivery, or outcome assessment. Daily screening and enrolment of eligible participants will be carried out by site investigators. After obtaining written informed consent and confirmation of eligibility, the senior surgeon will perform the allocation by opening sealed, opaque envelopes containing the group allocation, serving as the **sole custodian** of the envelopes. Participants assigned to the intervention group will be operated under 8 mmHg pneumoperitoneum pressure. Control group participants will be operated under pneumoperitoneum pressure (14 mmHg). All patients will receive 1g of intravenous paracetamol 30minutes before the operation’s end. Outcome assessments will be conducted by well-trained residents who are blinded to participants’ group assignments and data analysis. To minimize bias, these residents will not be involved in recruitment or intervention delivery. All assessors will undergo specific training to standardize data collection procedures and reduce inter-rater variability.

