### Secondary endpoints

**Change of VAS over time:** To evaluate the temporal evolution of VAS (at H6, H12 and H24), analysis of variance (ANOVA) with Bonferroni adjustment will be performed. This statistical approach is particularly suited to repeated measures data.Nausea and vomiting: Changes from baseline (H0) to the final time point (H4) will be analyzed within groups using paired ANOVA tests. Between-group comparisons of these changes will be performed using independent ANOVA tests.Duration of hospital stay: the mean hospital stays in each group (control vs intervention) will be compared using t-tests or non-parametric test U of Mann and Whitney when appropriate.Operative time: the mean operative time in each group (control vs intervention) will be compared using t-tests or non-parametric test U of Mann and Whitney when appropriate.Conversion rate: the frequency of conversion rate in each group will be compared by chi²test or fisher exact test when appropriate.30-day morbidity: the frequencies of each postoperative complication in each group will be compared by chi²test or fisher exact test when appropriate.

The statistical analysis will be conducted using SPSS version 26. Analyses will be performed by an independent investigator (CD in the authors’ list) blinded to treatment allocation, ensuring unbiased interpretation of the data.

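### The same investigator generates the randomisation sequence and analyses the data as a blinded analyst; analyst blinding is not secured as written

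*Protocol article*

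**What the plan says.** Four parts of the protocol article bear on this point.

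- **Trial implementation and coordination:** "The randomization sequence will be generated by (CD) not involved in recruitment, intervention delivery, or outcome assessment". Analysis is not among the activities from which this person is kept away.
- **Secondary endpoints (statistical methods):** "Analyses will be performed by an independent investigator (CD in the authors", by the same initials. This person is described as "blinded to treatment allocation, ensuring unbiased interpretation of the data".
- **Blinding:** "data analysts will be blinded to treatment assignment to ensure objectivity in statistical analyses and interpretation of results". Those who know the assignment are listed as "Only the surgeon, the anesthetist and the operating room nurse responsible for opening the allocation envelope", and the section adds: "These persons will not be involved in outcome assessment, clinical follow-up, or data analysis".
- **Randomization:** "The randomization sequence was generated using a table of random numbers", in fixed blocks of four, and patients were allocated in the order of the list.

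**The concern.** Whoever writes a randomisation list knows which arm each position carries. If the same person later analyses the data, blinding depends on a barrier between list and data file, and the article describes none. It nevertheless asserts the blinding twice and gives it as the reason why the interpretation will be unbiased.

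Two things are at stake. First, some analysis decisions remain open, and a blinded analyst is the protection that the article claims for them. Second, the trial report would carry over a statement about analyst blinding that the described conduct does not support.

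**Working it through.** The point contains no figure to recompute, and the sample size does not enter into it. The check sets the role assignments side by side.

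1. **Same person.** The sequence generator and the analyst carry the same initials, and the analysis text ties those initials to the authors' list. Nothing suggests two people.
2. **What the generator knows.** The list was made from a random-number table, so its author knew the arm at each position when writing it.
3. **Can a list position be linked to a patient?** Allocation was sequential, so enrolment order corresponds to list position. Anyone with the list and either enrolment numbers or surgery dates could recover assignments. With two arms, one patient matched with certainty decodes both labels.
4. **Is a barrier described?** The sealed opaque envelopes, held by the senior surgeon, hide the next assignment from those who recruit; they do not blind the author of their contents. The anonymised SPSS file (Study endpoints) removes identity, but the article does not say that arm labels are masked or that order and dates are dropped. No third party is named as holder of the list or as the one who recodes the arms.
5. **The protocol's own rule.** The Blinding section limits knowledge of the assignment to three operating-room roles and keeps those roles out of data analysis. The sequence generator is on neither side of that rule, yet wrote the assignments and does the analysis. Without a masking step, the Blinding, implementation and analysis texts do not fit together.
6. **What remains open at analysis.**
   - *Primary test.* The Primary endpoint text allows a t-test or Mann-Whitney as appropriate. Data analysis framework makes non-normality the trigger, without saying how it is judged.
   - *Per-protocol set.* It is named as a sensitivity analysis, but its membership is not defined.
   - *Exclusions after randomisation.* Eligibility criteria excludes patients with conversion to laparotomy or a retained Escat's drain. The analysis is to be by intention-to-treat, and conversion rate is itself a secondary endpoint. Someone must decide whether these patients are analysed, and both events can arise after allocation.
7. **What is already fixed.** Intention-to-treat as the main principle, the two-sided 5% level, the covariates of the adjusted analysis, the imputation method (fully conditional specification with predictive mean matching) and the two sensitivity analyses (complete-case and per-protocol) are all stated.

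Steps 6 and 7 mark out the exposure. The open details are not raised as omissions, since an analysis plan may settle them.

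**The case against.** A reader might infer that analyst blinding is simply absent and that all 170 assignments lie open to the analyst. The documents do not support that. They do not say that the generator kept the list, that the analysis file follows enrolment order, or that it contains numbers or dates that would allow a match. The envelopes are in the surgeon's sole keeping, and the generator has no part in recruitment, delivery or assessment. Arm labels recoded by a third party could restore much of the blinding, and such a step may exist unreported. This stands, and it limits the conclusion to blinding that is not secured.

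It can also be said that the analyst's freedom is small. The imputation method and the sensitivity analyses are named, per-protocol is only a sensitivity analysis, and choosing the more favourable of two tests by its p-value needs no knowledge of which arm is which. This stands too. Part of the exposure is a matter of pre-specification and would remain under A/B coding. It weighs least against the decision on converted or drained patients, where knowing the arm could matter most.

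Finally, the primary outcome is a pain score given by blinded patients to blinded residents. The overlap does not touch that, nor the concealment of the next assignment from recruiters.

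None of these arguments reconciles the passages. The article makes a positive claim that its own division of tasks undermines, so this is more than detail left to another document.

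**Conclusion.** The point holds as an inconsistency in the assignment of roles: one investigator both writes the allocation list and analyses the data under a claim of blinding, with no described safeguard. Analyst blinding is **not secured as written**. To say that it does not exist would go beyond the text.

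The size of any bias cannot be computed, and no scenario in the documents shows the primary result changing. Severity is moderate. The conclusion rests on reading the shared initials as one person and on the absence from the article of any masking step. If the full protocol or an analysis plan describes one, the remedy reduces to stating it in the article's terms.

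**What to change.** The list has already been generated, so the separation has to be made at the analysis end.

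**Preferred.** Another existing investigator, who has not seen the list, runs the analysis. The file has arms coded A/B and has enrolment numbers and surgery dates removed. The key is released only after data and code are locked.

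**If no swap is possible.** Before arm is merged with the data, lock with a date:

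- the rule for choosing the primary test;
- the analysis sets, including the per-protocol set and the handling of converted or drained patients under intention-to-treat;
- the full code.

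Then withdraw the analyst-blinding statement from the Blinding section and from the statistical text under Secondary endpoints, and report who held the list.

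The cost is one reassigned task or one dated code lock. Patients are not affected. Trial status places analysis after the last follow-up, expected by January 2026, so on the stated timeline either route can be completed before the analysis begins.

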#### Missing data.

The strategy is divided into two main areas: prevention and statistical treatment by imputation:

**1) Prevention**: To minimize the risk of missing data from the design and conduct of the trial, we took in account the following points:Easily measurable endpoints that are unlikely to be missing were chosen. Data collection is performed by a qualified professional (surgery resident).Patients are hospitalized and are unlikely to leave the hospital on the day of the procedure.The tolerable threshold for missing data is 5%. The Sample size of 140 patients, calculated in sample size and power section, was overestimated by 20% as per loss of follow-up and/or data discrepancies expectation. An overall sample size of 170 subjects will be enrolled in the study, divided into 85 experimental group vs. 85 placebo group.**2) Practical steps for dealing with missing data**: When missing data exists despite prevention efforts, it is essential to manage it in conjunction with intention-to-treat analysis, which is the preferred analysis method for Randomized Trials.

The most common situation is that the absence of data depends on the observed values of other variables, but not on the missing value itself: MAR (missing at random). The solution is then multiple imputation.

[The absence of data that depends on the missing value itself MNAR (missing Not at random) is exceptional in the design of this trial: primary outcome is postoperative abdominal pain assessed using the Visual Analog Scale (VAS) at 6 hours after surgery].

**3)** A **sensitivity analysis** involves repeating the main analysis using different methods of handling missing data to verify whether the conclusions of the trial remain the same.

#### Data analysis framework.

All analyses will follow the intention-to-treat principle. The primary outcome (VAS pain score at 6 hours) will be compared between groups using an independent t-test or a Mann–Whitney U test if non-normal. An adjusted analysis using ANOVA will be performed with age, sex, BMI, ASA class, and operative time as covariates. Repeated measures of pain (6, 12, and 24 hours) will be analyzed using analysis of variance (ANOVA) with Bonferroni adjustment. Categorical variables, including postoperative nausea and vomiting and complications, will be compared using χ² or Fisher’s exact tests. Continuous secondary outcomes will be analyzed using t-tests or appropriate non-parametric methods. Missing data will be addressed using multiple imputation (fully conditional specification with predictive mean matching), with sensitivity analyses including complete-case and per-protocol analyses. All tests will be two-sided with a significance level of 0.05. Statistical analyses will be performed using SPSS version 26.

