**Methods:**

This is a single-center, randomized, controlled, double-blind trial. Consecutive Adult patients scheduled for elective laparoscopic cholecystectomy will be randomized in a 1:1 ratio to receive either low-pressure (8 mmHg) or standard-pressure (14 mmHg) pneumoperitoneum. The primary outcome is postoperative abdominal pain assessed using the Visual Analog Scale (VAS) at 6 hours after surgery. Secondary outcomes include VAS pain scores at 12 and 24 hours, postoperative nausea and/or vomiting, postoperative hospital stay and postoperative 30-day morbidity. The enrollment of patients will be done between November 12, 2024 to December 31, 2025.

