### Study endpoints

#### Primary endpoint.

Postoperative pain at 6th postoperative hour (H6): defined as abdominal and/or interscapular pain measured by a Visual Analog Scale (VAS) as following, from 0 to 10: 0 no pain, 5 moderate pain, 10 worst possible pain.

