### Statistical methods

#### Sample size and power.

Using the VAS scale, the mean value of abdominal pain after laparoscopic cholecystectomy with a pressure of 14 mm Hg is estimated in the literature at **4.1 + /-1.8** (H6) [9]. We hypothesize that patients in the low-pressure group will experience significantly lower postoperative pain compared to those in the standard-pressure group (14 mm Hg), with no increase in postoperative morbidity. The difference of means (Δ) is estimated to “01”. For a power level of 90%, a significance level of 5% and a two-way comparison between the two arms of the study, 70 patients/group are needed, i.e., 140 in all. Sample size was overestimated by 20% as per loss of follow-up and/or data discrepancies expectation. An overall sample size of 170 subjects will be enrolled in the study, divided into 85 experimental group vs. 85 placebo group [10]. Allocated study subjects were randomly assigned by, using simple 1:1 non-stratified sequence and a block size of 4.

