### Primary endpoint

The primary endpoint is the postoperative pain at 06 hours, assessed by VAS will be compared by Student t test or non-parametric test U of Mann and Whitney when appropriate.

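### The 6-hour primary comparison is not stated consistently: the pain site differs between sections, and the test is chosen from the observed distribution although the trial is powered on a difference of means

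*Protocol article*

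**What the plan says.** **Pain site.** Under Study endpoints, the primary endpoint at 6 hours is "defined as abdominal and/or interscapular pain measured by a Visual Analog Scale (VAS) as following, from 0 to 10". It is a single score, and the 12- and 24-hour endpoints use the same definition. The Methods part of the abstract says "The primary outcome is postoperative abdominal pain assessed using the Visual Analog Scale (VAS) at 6 hours after surgery", and the Missing data section repeats that the "primary outcome is postoperative abdominal pain assessed using the Visual Analog Scale (VAS) at 6 hours after surgery". Sample size and power also works from the abdominal site: "the mean value of abdominal pain after laparoscopic cholecystectomy with a pressure of 14 mm Hg is estimated in the literature at" 4.1 with SD 1.8.

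**Test.** In the statistical section on the primary endpoint, the 6-hour score "will be compared by Student t test or non-parametric test U of Mann and Whitney when appropriate". In Data analysis framework it "will be compared between groups using an independent t-test or a Mann–Whitney U test if non-normal". Neither section gives a normality criterion. The sample size rests on a difference of means of 1 point, two-sided 5%, 90% power.

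**Related analyses.** Data analysis framework adds an adjusted ANOVA with age, sex, BMI, ASA class and operative time, but does not call it primary. It also plans multiple imputation, with complete-case and per-protocol sensitivity analyses.

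**The concern.** A primary comparison needs one variable and one summary of the treatment effect, both fixed before the data are seen. Here neither is settled on paper.

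- **Variable.** Pain at either site and abdominal pain are different outcomes. If the reduction came mainly from interscapular pain, the abstract's wording would present it as a reduction in abdominal pain. The planning SD may also not describe the score in the endpoint definition.
- **Summary.** A t-test addresses the difference in means for which the trial was sized. Mann–Whitney addresses whether scores in one arm tend to rank below those in the other. A rule that picks between them from the observed distribution leaves the primary hypothesis open until the data are in. If it lands on Mann–Whitney, the primary p-value does not estimate the planned 1-point difference, and it cannot be pooled directly over imputations, since standard pooling needs an estimate and its standard error.

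**Working it through.** **Step 1. Pain site, section by section.**

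| Section | Site |
|---|---|
| Study endpoints, primary endpoint | abdominal, interscapular or both, one VAS |
| Study endpoints, 12 and 24 hours | same as above |
| Abstract, Methods | abdominal |
| Missing data | abdominal |
| Sample size and power | abdominal (4.1, SD 1.8) |

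The conflict is in the text and needs no calculation.

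**Step 2. Reproduce the sample size.** Inputs from Sample size and power: Δ = 1, SD = 1.8, two-sided α = 0.05, power 0.90.

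n per arm = 2 (1.960 + 1.282)² × 1.8² / 1² = 2 × 10.51 × 3.24 = 68.1, rounded up to 69. The noncentral t version gives 69.06, rounded up to 70. The stated 70 per group reproduces, and it is a calculation for a difference of means. Noncentral t power is 90.4% at 70 per arm and 95.0% at 85.

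If Mann–Whitney were the fixed test and the data normal (asymptotic relative efficiency 0.955), the need would be 69.06 / 0.955 = 72.3, so 73 per arm. Enrolment of 85 per arm covers this.

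**Step 3. What the site conflict means for the planning figure.** Only the SD enters the formula, not the control mean. Solving for the SD at 90% power, SD = √(n / (2 × 10.51)): 1.82 with 70 scores per arm and 2.01 with 85. The document gives no SD for the combined score, so whether it falls inside that margin is unknown.

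**Step 4. What the test rule does.** Simulation with 4,000 trials per setting, means 4.1 and 3.1 (or both 4.1), SD 1.8. The following are assumptions, because the protocol states none of them: the rule switches to Mann–Whitney if Shapiro–Wilk rejects at 5% in either arm; scores are either a normal clipped to 0–10 or a scaled beta; recording is to 0.1 or to whole points.

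85 per arm, true difference 1:

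| Shape, recording | t-test power | Mann–Whitney power | Two-stage power | Switches | Tests disagree |
|---|---|---|---|---|---|
| Normal, 0.1 | 95.0% | 94.3% | 94.9% | 23% | 1.7% |
| Normal, whole | 94.8% | 94.3% | 94.3% | 100% | 1.9% |
| Beta, 0.1 | 94.3% | 95.1% | 95.1% | 89% | 1.6% |
| Beta, whole | 94.4% | 94.9% | 94.9% | 100% | 1.3% |

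With no true difference at 85 per arm, type I error across the three procedures and four settings lies between 4.5% and 5.6%. The rule then switches in 8%, 99.7%, 42% and 100% of trials, in the same row order. At 70 per arm the tests disagree in 1.4% to 3.1% of trials.

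Two readings follow. The t-test holds its level without normality at these sizes, so the check protects against nothing here. And which test becomes primary depends heavily on features the protocol does not fix.

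**The case against.** The case on the other side is substantial, and much of it stands.

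- *Error rates are unaffected.* This stands. Power and type I error barely move, and the tests seldom disagree. A reader might infer that the two-stage rule weakens the trial or inflates false positives; the simulation does not support that.
- *The mean difference is compared anyway.* This stands in part. A reader might infer that the planned contrast may never be tested. The adjusted ANOVA compares arm means whatever the distribution, and the Statistical analysis section reports means and SDs unless a variable is skewed. But that ANOVA is not primary. It also adjusts for operative time, which is measured after randomisation, is itself a secondary endpoint and may be affected by pressure. It does not replace the powered contrast.
- *Rounding decides the test.* A reader might infer this from the near-100% switch rate with whole-point recording. The documents do not state whole-point recording or a formal normality test. With recording held at 0.1 points, the switch rate still runs from 23% to 89% with shape alone.
- *The site is not chosen after the data.* This stands. There is one formal definition with one score, and no provision for separate site scores or a later choice between them. The abdominal-only statements may be shorthand. That makes this a wording conflict plus a caveat on the planning SD, not post hoc selection.
- *Imputation pooling is a detail.* Largely fair. A rank-based effect with a standard error can be pooled, and the tolerable level of missing data is set at 5%. What remains is that the p-value named as primary does not pool directly.

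**Conclusion.** The point holds as a should-fix on clarity of the estimand and on pre-specification. Two things are stated wrongly rather than left out: the pain site conflicts between sections, and the primary test is made conditional on the observed data while the trial is sized on a mean difference.

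The effect on operating characteristics is small: power 94–95%, type I error about 5%, and disagreement between the tests in about 1–2% of trials at 85 per arm. The switch rate of about 23% to 100% with a true 1-point difference is conditional on the assumed Shapiro–Wilk rule, the two data shapes and the two recording resolutions. It shows that the choice of test is unpredictable, not that any one outcome is certain. The sample size is correct for its stated inputs. Whether an SD of 1.8 also fits the combined-site score cannot be judged from the document.

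**What to change.** Before any unblinded analysis:

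1. Use one pain-site definition throughout, namely the score in the primary endpoint definition, after confirming that this is what the data collection form records. Correct the abstract and the Missing data section to match. Note in Sample size and power that the planning mean and SD are for abdominal pain.
2. Fix the primary analysis as the difference in mean 6-hour VAS with its 95% CI, pooled over imputations. Either the t-test or a linear model with the baseline covariates already listed (age, sex, BMI, ASA class) would do. Choose one now, and leave operative time out.
3. Report Mann–Whitney as a sensitivity analysis whatever the distribution, and delete the conditional wording in both sections.

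The cost is wording only; the sample size stays as it is. Switching to a new abdominal-only score is not a comparable option. The Trial status section says recruitment is under way, so patients already enrolled would lack the primary score.

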### Data collection

#### Baseline assessment (at admission).

Prior to group allocation, each participant’s sociodemographic data (such as age, gender, Body Mass index), baseline characteristics including comorbidities, American Society of Anesthesiologist (ASA) score, preoperative clinical examination, preoperative biological tests, preoperative ultrasound data, and surgical exploration data after trocar placement will be recorded.

Following this assessment, participants will be randomized into one of two study groups.

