#### During laparoscopic cholecystectomy.

The presence of eventual adhesions, difficult dissection, bleeding, biliary injury, realization of cholangiography, placement of Escat’s drain, placement of drainage, operation time were recorded.

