## Discussion

This trial aims to investigate the role of low pressure pneumoperitoneum in reducing postoperative pain after laparoscopic cholecystectomy. We hypothesize that low pressure pneumoperitoneum at 8 mmHg reduces postoperative pain, without increasing operation time or postoperative morbidity.

If low pressure pneumoperitoneum is shown to effectively improve postoperative pain after LC, it could lead to several positive outcomes. This includes a potential reduction in the consumption of postoperative pain killer and the duration of hospital stay. In fact, one of the most reported causes of failure of ambulatory cholecystectomy is postoperative pain [11]. These improvements could translate into significant cost-savings for healthcare systems.

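### The adjusted analysis of 6-hour pain includes operative time, a post-allocation outcome, so it may not estimate the total effect of pressure

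*Protocol article*

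**What the plan says.** In the protocol article, Data analysis framework, the primary outcome "will be compared between groups using an independent t-test or a Mann–Whitney U test if non-normal". The next sentence adds a supplementary model: "An adjusted analysis using ANOVA will be performed with age, sex, BMI, ASA class, and operative time as covariates". The Primary endpoint paragraph of the statistical section mentions only the unadjusted test.

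Elsewhere the protocol treats operative time as a result of surgery:

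- During laparoscopic cholecystectomy lists it among the intraoperative data: "placement of drainage, operation time were recorded".
- Study endpoints names it as a secondary endpoint, and the statistical section compares it between arms: "the mean operative time in each group (control vs intervention) will be compared using t-tests".
- The Abstract and Discussion make it part of the hypothesis. The Discussion says that low pressure "reduces postoperative pain, without increasing operation time or postoperative morbidity".

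No rationale is given for using it as a covariate, and the model is not labelled as a mediation or direct-effect analysis.

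**The concern.** The aim is to compare pain under two pressure strategies, and the protocol says that all analyses follow intention to treat. The estimate that fits this is the total effect of allocation, through whatever route it acts. Age, sex, BMI and ASA class are fixed before allocation, so adjusting for them leaves that target alone. Operative time is not fixed before allocation. If working at 8 mmHg makes the operation longer and a longer operation hurts more, part of the effect of pressure on pain runs through operative time. Holding operative time constant takes that part out.

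In that scenario the part removed is unfavourable to low pressure, so the adjusted figure moves in favour of the experimental arm. This is the only covariate-adjusted model of the primary outcome in the document, and it is tested at the same 0.05 level. If it differed from the unadjusted result, a reader could take it for the better-controlled estimate when it answers a different question.

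There is a second difficulty. Operative time and pain may share causes that the model does not contain, such as a difficult dissection. The adjusted coefficient would then not be a clean direct effect either.

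**Working it through.** **1. The plan's own figure.** Inputs from Sample size and power: SD 1.8, difference 1 VAS point, two-sided 5%, power 90%.

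- Normal approximation: n per arm = 2 × (1.960 + 1.282)² × 1.8² / 1² = 2 × 10.51 × 3.24 = 68.1, so 69.
- Exact noncentral t: 70 per arm, with power 90.4%.

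The stated 70 per group is reproduced. It rests on the unadjusted comparison and does not depend on any covariate.

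**2. Timing.** Baseline assessment ends with "Following this assessment, participants will be randomized into one of two study groups". The latest point before allocation that it mentions is exploration after trocar placement. Operative time is known only when the operation ends, after the procedure has been run at the assigned pressure. On any reading of the allocation step it is a post-allocation variable.

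**3. Formula.** Let effects be low minus standard pressure, so that a negative value is a benefit. Let d be the arm difference in mean operative time, b the within-arm slope of VAS on operative time, and r the within-arm correlation. In a linear model:

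- adjusted coefficient = total effect − b × d
- b = r × 1.8 / SD of operative time
- hence the shift b × d = (d in SD units) × r × 1.8

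Only the 1.8 comes from the protocol. The values of d and r below are assumptions.

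| d (SD) | r | Shift b × d | Adjusted if total is −1.0 | Adjusted if total is 0 |
|---|---|---|---|---|
| 0 | any | 0 | −1.00 | 0 |
| 0.2 | 0.2 | 0.2 × 0.2 × 1.8 = 0.072 | −1.07 | −0.07 |
| 0.5 | 0.3 | 0.5 × 0.3 × 1.8 = 0.27 | −1.27 | −0.27 |
| 0.75 | 0.3 | 0.75 × 0.3 × 1.8 = 0.405 | −1.405 | −0.405 |
| −0.5 | 0.3 | −0.27 | −0.73 | +0.27 |

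The last row is the case in which low pressure shortens surgery. The benefit is then understated.

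**4. Simulation.** 70 per arm, 3,000 runs per scenario, assumed operative-time SD 20 minutes, operations 0 to 15 minutes longer at 8 mmHg, r from 0.1 to 0.3. The mean adjusted estimates agreed with the formula to within about 0.01. With a true total effect of zero:

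- No difference in operative time: the adjusted test rejected in 4.8% to 4.9% of trials.
- 5 minutes, r = 0.1: 4.9%.
- 10 minutes, r = 0.3: 14.7%.
- 15 minutes, r = 0.3: 25.1%.
- The unadjusted test stayed between 4.4% and 5.6% in all these scenarios.

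**The case against.** The strongest reply is that this is a supplementary model. The primary test is the unadjusted t-test or Mann-Whitney U. The sample size was calculated for that test, and nothing in the protocol gives the adjusted model priority. The protocol expects no increase in operative time, and if that is right the shift is zero. Operative time is also a plausible marker of a hard operation, so including it could gain precision. At r = 0.3 the residual variance falls to 1 − 0.3² = 0.91 of its unadjusted value.

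Most of this stands, and it limits the point. Three stronger readings might be inferred, and the documents support none of them:

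- **That the primary analysis is compromised.** It contains no covariates and is unaffected. Nothing calls the adjusted model confirmatory.
- **That longer operations would be concealed.** Operative time has its own between-arm comparison, and any pain that longer surgery causes is captured by the unadjusted VAS test. Only the adjusted pain estimate could mask it.
- **That adjustment necessarily shrinks the benefit.** Whether it shifts the estimate at all, and in which direction, depends on how pressure changes operative time and how operative time relates to pain. In the feared case the benefit is enlarged.

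What does not stand is reliance on the hypothesis of no increase. The trial is testing that hypothesis, so a model of the primary outcome should not need it to be true. The possible gain in precision does not justify a covariate that can change what is being estimated.

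**Conclusion.** The point holds for the supplementary adjusted analysis of VAS at 6 hours, and only there. Operative time is measured after allocation, is a declared secondary endpoint, and is a quantity that the trial asks whether low pressure increases. If pressure changes operative time and operative time affects pain, the adjusted coefficient is not the total intention-to-treat effect.

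The size cannot be derived from the documents. Under the assumptions shown it runs from nothing, through about 0.07 points, to about 0.27 points, which is roughly a quarter of the planned 1-point difference. The more extreme input of 0.75 SD gives about 0.41. The direction favours low pressure if it lengthens surgery and longer surgery raises pain, and reverses if low pressure shortens surgery. This is a should-fix. It does not threaten the primary result.

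**What to change.** In Data analysis framework, delete operative time from the covariate list. Describe the adjusted model as a linear model (ANCOVA) with arm, age, sex, BMI and ASA class. Keep operative time as an outcome. If its role in pain is of interest, use it only in a separate model labelled as an exploratory mediation analysis.

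Do not put adhesions or other intraoperative findings in its place unless they are recorded before the allocation envelope is opened. The protocol does not show that they are. Baseline assessment says that "surgical exploration data after trocar placement will be recorded" before randomisation but does not name adhesions, and it stands under a heading that refers to admission. Adhesions are listed with the data collected during surgery. Trial implementation and coordination has the envelope opened after consent and confirmation of eligibility, without placing this after trocar insertion.

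The cost is one line of text. No new data are needed, and the 70 per group is unchanged. Trial status puts the analysis after the end of follow-up, so the change should be dated and made before any results by arm are seen.
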